#### **9.3.2 Secondary analysis of the primary endpoint**

Although the study is primarily powered for the comparison between the RUTF and control group the other groups will be compared as well, keeping in mind that the sample size might not be large enough to obtain significant results.

Since there are three interventional groups to be compared, a hierarchical test procedure will be used to account for multiplicity.

1) In a first step, RUTF will be compared to the control group, which is described above as analysis of primary outcome

If the RUTF group is not significantly different at a 0.05 level (two-sided test), the hierarchical procedure is stopped (all following analyses will be considered explorative). If the RUTF group is significantly different at a 0.05 level, the hierarchical procedure is continued with step 2.

2) In the second step, MNP will be compared to the control group.  
The hypotheses in this step are

$$H_0: \text{rate}_{\text{MNP}} = \text{rate}_{\text{Control}}$$

vs.

$$H_1: \text{rate}_{\text{MNP}} \neq \text{rate}_{\text{Control}}$$

where  $\text{rate}_{\text{MNP}}$ =rate of “negative nutritional outcome” in the children in the MNP group, and  $\text{rate}_{\text{Control}}$ =rate of “negative nutritional outcome” in the children in the placebo to MNP group.

If the treatment factor is not significant at a 0.05 level (two-sided test), the hierarchical procedure is stopped (all following analyses will be considered explorative). If the treatment factor is significant at a 0.05 level, the hierarchical procedure is continued with step 3.

3) In the third step, RUTF will be compared to MNP (non-inferiority test).  
The hypotheses in this step are

$$H_0: \text{rate}_{\text{RUTF}} - \text{rate}_{\text{MNP}} > -\square$$

vs.

$$H_1: \text{rate}_{\text{RUTF}} - \text{rate}_{\text{MNP}} \leq -\square$$

where  $\text{rate}_{\text{RUTF}}$ =rate of “negative nutritional outcome” in the children in the RUTF group,  $\text{rate}_{\text{MNP}}$ =rate of “negative nutritional outcome” in the children in the MNP group, and  $\square$ =inferiority margin.

As non-inferiority margin, a  $\square$  of 2% will be used (i.e. allowing a slightly worse result in the MNP compared to the RUTF group). The third step will be tested at a 0.025 level (one-sided test), by a one-sided 97.5% confidence interval of the difference in rates between the RUTF and the MNP group.

In addition, in case of significant and/or relevant differences of baseline values additional adjustment(s) for these factors will be performed within the model described above (in models with and without interaction), to address the potentially confounding or effect modifying effect of other variables. These variables include age (in months and binary: <36 months,  $\geq 36$  months), gender, breastfeeding practices, cough, underlying illnesses, socio-economic factors, food availability, length of illness before visiting MSF clinic, other health support sought during study, season during which child was in the study.

The amount and pattern of missing data of the primary endpoint will be checked by a person blinded to treatment allocation, and a decision based upon the result of this check will be made as to whether and how the imputation of missing primary endpoint data will be performed.

Additionally, the 6-months follow-up period will be split and analysed separately for 1 month periods with the method described above.

The analysis of the primary endpoints will also be repeated as described above separately for children with no malnourishment at time of entry into study and children with moderate malnourishment at time of entry into study.

The analysis of the primary endpoint will be repeated as described above for the per protocol population.

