## **8.8 Endpoints**

### **8.8.1 Primary endpoint**

The primary endpoint is “negative nutritional outcome (NNO)” of a child within the 6 months follow-up period. The incidence of a negative nutritional outcome will be defined according to the baseline nutritional status.

- i) for children with no malnourishment at time of entry into study, “negative nutritional outcome” is defined as progression to moderate or severe malnourishment

Thus, the event of a child reaching a “negative nutritional outcome” at least once within 6 months of follow-up period will be compared between the three study groups.

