A Poisson regression with a binary independent group variable with proportion of 0.5 (equal allocation ratio) using a sample of 1320 observations (i.e. 660 per group) achieves 80% power at a 0.05 significance level to detect a incidence rate ratio of at least 0.7 (i.e. incidence rates of 0.14 (intervention rate) vs. 0.2 (baseline rate)).

To account for an assumed drop-out rate of approximately 10%, 734 children will be included in each group (i.e. 2202 in total for all three groups).

The sample size estimation is based on the first two hierarchical test hypotheses (while the third hypothesis comparing RUTF with MNP for non-inferiority is considered explorative). Sample size estimations are performed with PASS 2008 (Version 08.0.13, Windows XP) and SAS version 9.2 (SAS Institute, Cary, NC, USA).

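### The null and alternative hypotheses of the RUTF–MNP non-inferiority step are reversed in section 9.3.2

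*Protocol*

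**What the plan says.** Section 9.3.2 of the protocol sets out a three-step hierarchy: RUTF against control, then MNP against control, then RUTF against MNP. Each step is reached only if the one before it is significant. The third is introduced as "In the third step, RUTF will be compared to MNP (non-inferiority test"). For the margin, a value "of 2% will be used", with the gloss "allowing a slightly worse result in the MNP compared to the RUTF group". On the error rate: "The third step will be tested at a 0.025 level (one-sided test"), using a one-sided 97.5% confidence interval for the difference in rates. The section does not say which limit is compared with the margin.

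Write R and M for the rates in the RUTF and MNP groups and δ for the margin. The symbol itself did not survive in the text available for review. The displayed hypotheses are then:

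- H0: R − M > −δ
- H1: R − M ≤ −δ

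The rate is that of a negative nutritional outcome. Section 8.8.1 defines this, for a child not malnourished at entry, as "progression to moderate or severe malnourishment". A higher rate is worse.

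Section 9.1 says of this comparison that "the third hypothesis comparing RUTF with MNP for non-inferiority is considered explorative", in a sentence about which hypotheses the sample size rests on.

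**The concern.** In a non-inferiority test, the claim to be established belongs in the alternative. Here H1 rearranges to M ≥ R + δ, so the alternative states that the powder is worse than RUTF by at least the margin. Non-inferiority of MNP sits in the null, where rejection can only count against it. The formulae contradict both the name of the test and the sentence that explains the margin.

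The comparison matters to the trial. Section 1.5 asks whether the macronutrient part of RUTF is needed at all, and section 11.3 contrasts the expense of RUTF with the low cost of a powder. An analyst must either follow formulae that cannot deliver the intended conclusion or depart from a prespecified hypothesis without authority from the text. If a rejection under the written hypotheses were reported under the step's own name, it would be reported as the opposite of what it shows.

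**Working it through.** **The plan's own figure first.** Section 9.1 states 1320 observations for two groups (660 each), with rates of 0.20 and 0.14 per 6 months, two-sided 0.05 and 80% power. The usual formula for Poisson regression with one balanced binary covariate is

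N = (1.960·√V0 + 0.842·√V1)² / (0.20·(ln 0.7)²), with V0 = 4 and V1 = 2 + 2·(0.20/0.14) = 4.857.

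This gives N = 1311, and 80.3% power at 1320. Drop-out: 660/0.9 = 733.3, rounded up to 734. Both stated figures are reproduced. The protocol states no figure for step 3.

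**Direction of the hypotheses.**

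1. A higher rate is worse (section 8.8.1).
2. MNP may be slightly worse than RUTF (section 9.3.2), so non-inferiority is M < R + δ, that is R − M > −δ.
3. The protocol writes this as H0 and its complement as H1.
4. Taking RUTF as the tested product does not help. H1 would then say that RUTF is better than MNP by at least δ, which is superiority by a margin and not non-inferiority.
5. The inequality signs, minus signs and order of the arms are legible, and H0 and H1 are exact complements. Only the margin symbol is lost, so this is not a text-reading artefact. No other section states the hypotheses the right way round.

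**Rejection probabilities with step 3 run alone.** Inputs: n = 660 per group and R = 0.14 (section 9.1); δ = 0.02 and one-sided 0.025 (section 9.3.2). Each child is assumed to contribute one full 6-month unit, and 2% is read as an absolute difference per 6 months. With d = R − M and SE = √((R + M)/n):

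- as written, reject when the upper limit is ≤ −0.02: P = Φ((−0.02 − d)/SE − 1.960)
- corrected, reject when the lower limit is > −0.02: P = Φ((d + 0.02)/SE − 1.960)

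Equal rates (M = 0.14): SE = √(0.28/660) = 0.0206. As written, Φ(−0.971 − 1.960) = 0.0017. Corrected, Φ(0.971 − 1.960) = 0.161.

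MNP at the control rate (M = 0.20): SE = √(0.34/660) = 0.0227 and d = −0.06. As written, Φ(0.04/0.0227 − 1.960) = 0.42. Corrected, Φ(−0.04/0.0227 − 1.960) = 0.0001.

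| MNP rate | Rejects H0 as written | Rejects H0 corrected |
|---|---|---|
| 0.14 (equal) | 0.2% | 16% |
| 0.16 (at the margin) | 2.5% | 2.5% |
| 0.18 | 15% | 0.2% |
| 0.20 (assumed control rate) | 42% | 0.01% |

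As written, the chance of rejection rises as MNP gets worse, which is the reverse of a non-inferiority test. For example, 92 events among 660 on RUTF and 165 among 660 on MNP give d = −0.111 with limits −0.158 to −0.063. The written H0 is rejected although MNP is clearly worse. The corrected H0 is not.

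**Through the gates.** Step 3 is formally reached only if steps 1 and 2 are both significant. The whole hierarchy was simulated with Poisson counts, 660 per group, control 0.20, RUTF 0.14 and two-sided Wald tests at 0.05 in steps 1 and 2.

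- M = 0.14: step 3 is reached and H0 rejected in about 0.02% of trials as written, against about 8% corrected.
- M = 0.20: step 3 is reached in about 3.1% of trials, and H0 is rejected as written in about 0.8% of all trials.

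**The case against.** The strongest reply concerns the size of the consequence. The hierarchy protects against most of it. If MNP is no better than control, step 2 will rarely be significant, so the 42% describes the step run on its own and not the procedure in section 9.3.2. A reader might infer from the table that the plan would often endorse an inferior powder. The documents do not support that: through the gates the figure is about 0.8%. The words of the section are also right even though the formulae are not. An analyst guided by them would compare the lower limit with −2%, and an interval lying wholly below −2% would be visible as bad news for MNP. Step 3 is last in the order, is not powered, and serves a secondary objective.

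All of that stands, and it lowers the severity. It does not remove the error. The interval sentence does not name the deciding limit, so nothing in the protocol overrides the formulae. Section 9.3.2 also lets later steps be analysed as explorative after a stop, where the same hypotheses would apply without the protection of the gates. A later analysis plan could put this right only by contradicting the protocol.

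A reader might be tempted to add four further faults, none of which the documents bear out:

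- **The margin is a difference while the model gives ratios.** Section 9.3.1 names no link, and section 9.3.2 asks expressly for an interval on the difference. How to obtain it is for the analysis plan.
- **The margin has no time unit.** Section 9.1 works per 6 months throughout, and 2% reads naturally on that scale.
- **Sections 9.1 and 9.3.2 conflict on whether step 3 is explorative.** The remark in 9.1 concerns what the sample size is based on. A gated third step can control its error rate without being powered.
- **Power of 16% is a defect.** Section 9.3.2 already warns that the sample may be too small for comparisons other than RUTF against control.

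**Conclusion.** The point holds. The hypotheses of step 3 are stated the wrong way round, and the contradiction lies within section 9.3.2 itself. The main practical loss is that equal products would almost never be declared non-inferior: 0.2% against 16% with the step run alone, and about 0.02% against 8% through the gates. The opposite danger, a rejection that means inferiority but carries the non-inferiority label, is real in principle and small in the formal procedure.

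The probabilities assume 660 children with full 6-month follow-up in each group, the protocol's planning rates, a normal approximation, and a margin of 0.02 per 6 months. The direction of the error depends on none of these. The primary RUTF–control test, step 2 and the sample size are untouched, so the severity is moderate.

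**What to change.** In section 9.3.2, step 3, replace the hypotheses with:

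- H0: rate(RUTF) − rate(MNP) ≤ −0.02
- H1: rate(RUTF) − rate(MNP) > −0.02

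State that the rates are per 6 months, as in section 9.1. Add the decision rule: MNP is declared non-inferior to RUTF only if the lower one-sided 97.5% confidence limit for rate(RUTF) − rate(MNP) is above −0.02. Carry the same wording into the statistical analysis plan, and make the change before the allocation is revealed. It costs a few lines of text and does not alter the design, the data collected or the number of children.

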#### **9.3.1 Primary analysis of the primary endpoint**

The primary endpoint is “negative nutritional outcome” of a child within the 6 months follow-up period as defined in section 8.8.1. The incidence rate (in formulae below referred to simply as ‘rate’) of “negative nutritional outcome” will be computed as the number of events divided by total observed person-time in each treatment group. As an “event” the first time a child reaches a negative nutritional outcome will be used. The primary analysis of the primary endpoint will be performed on the intention to treat population with no imputation of missing data.

In the primary analysis, RUTF will be compared to the control group.  
The hypotheses in this step are

$$\begin{aligned} H_0: \text{rate}_{\text{RUTF}} &= \text{rate}_{\text{Control}} \\ \text{vs.} \\ H_1: \text{rate}_{\text{RUTF}} &\neq \text{rate}_{\text{Control}} \end{aligned}$$

where  $\text{rate}_{\text{RUTF}}$  = rate of “negative nutritional outcome” in the children in the RUTF group, and  $\text{rate}_{\text{Control}}$  = rate of “negative nutritional outcome” in the children in the control group.

The comparison of rates among the treatment groups will be performed by a Poisson regression model, adjusted for nutritional status at enrolment (fixed effect) and will be performed within one model including the three intervention groups with contrasts for each two-group comparison. Tests will be two-sided with a significance level of 0.05.

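### Step 3 of the test hierarchy has a 2% margin without a time unit and hypotheses printed in reverse, and it can be reached when a supplement is worse than control

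*Protocol*

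**What the plan says.** Protocol section 9.3.1 states that the incidence rate "will be computed as the number of events divided by total observed person-time in each treatment group" and that the word rate has this meaning in the formulae that follow. The unit of person-time is not given. For the primary comparison, "Tests will be two-sided with a significance level of 0.05".

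Section 9.3.2 sets out a three-step hierarchy.

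- **Step 1, RUTF versus control.** "If the RUTF group is significantly different at a 0.05 level, the hierarchical procedure is continued with step 2". No direction is required.
- **Step 2, MNP versus control.** The same rule applies: a two-sided significant treatment factor leads on to step 3.
- **Step 3, RUTF versus MNP, non-inferiority.** The null hypothesis is printed as rate_RUTF − rate_MNP > −margin and the alternative as rate_RUTF − rate_MNP ≤ −margin. The margin is described as "of 2% will be used (i.e. allowing a slightly worse result in the MNP compared to the RUTF group". Step 3 has its own one-sided level of 0.025, and the decision is made "by a one-sided 97.5% confidence interval of the difference in rates between the RUTF and the MNP group".

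Section 9.1 gives the only time unit for the rate: a control incidence of 0.201 over 6 months, rounded to 0.20, against 0.14. It also says that the third hypothesis is regarded as explorative.

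**The concern.** A difference between two person-time rates carries a unit, so a margin of 2% means different things per child-month, per 6 child-months and per child-year. The protocol fixes the margin as a number but leaves its meaning to whoever codes person-time. Section 9.3.2 also repeats the analysis for separate 1-month periods by the same method, without saying what the margin would then be.

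Two further defects sit in the same procedure. The hypotheses, taken as printed, would make a rejection evidence that MNP is inferior. And because steps 1 and 2 ask only for a two-sided significant difference, a supplement that does worse than control also moves the sequence forward. MNP could then be declared non-inferior to a RUTF arm that had itself done harm.

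At stake is how the only formal RUTF versus MNP comparison can be interpreted. The primary comparison is not touched.

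**Working it through.** **Inputs (Protocol 9.1, 9.3.1, 9.3.2).** Rates of 0.20 (control) and 0.14 (each supplement) per 6 months; 660 per arm after drop-out; two-sided 0.05 in steps 1 and 2; one-sided 0.025 in step 3; margin 2%.

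**1. The plan's own figures.** Incidence: (0.155/10 + 0.072/4) × 6 = 0.201, as stated. For the sample size I used the Signorini formula for Poisson regression with a "binary independent group variable with proportion of 0.5 (equal allocation ratio"):

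N = (z_α√V0 + z_β√V1)² / (rate0 × (ln RR)²), with V0 = 1/(0.5 × 0.5) = 4 and V1 = 1/0.5 + 1/(0.5 × 0.7) = 4.857.

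N = (1.96 × 2 + 0.842 × 2.204)² / (0.20 × 0.1272) ≈ 1311, against the stated 1320. Power at 1320 is 80.3%. Drop-out: 660/0.9 = 733.3, so 734. The stated figures reproduce. None is given for step 3.

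**2. What 2% means under each unit.** Only the 6-month unit has support in the protocol; the other two are assumptions that show the range. With both supplements at 0.14 per 6 months and full follow-up:

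SE = √(0.14/660 + 0.14/660) = 0.0206; probability of passing = Φ(margin/SE − 1.96).

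| Unit of the 2% | Margin per 6 months | Equivalent rate ratio at 0.14 | Step 3 alone passes |
|---|---|---|---|
| per child-year | 0.01 | 1.07 | 7% |
| per child-6-months | 0.02 | 1.14 | 16% |
| per child-month | 0.12 | 1.86 | nearly 100% |

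On the 6-month reading the confidence limit lies 1.96 × 0.0206 = 0.040 from the estimate, twice the margin. MNP would have to be observed about 0.020 better than RUTF to pass.

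**3. Direction of the hypotheses.** A higher rate is worse. If MNP equals RUTF, the difference RUTF − MNP is 0, which is above −0.02 and so falls under the printed null. If RUTF is 0.14 and MNP 0.20, the difference is −0.06, which falls under the printed alternative. Rejecting the printed null therefore shows MNP worse by at least the margin. In simulation this happens in 42% of trials at 0.14 versus 0.20. The margin's explanation, which tolerates a slightly worse MNP result, requires the opposite arrangement.

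**4. Continuation on harm.** Under no effect, each two-sided 0.05 test is significant towards harm in about 2.5% of trials. The two tests share the control arm, so the joint probability was simulated (400,000 trials, 660 per arm, 0.20 in all arms): both are significant in 0.9%, of which 0.4 points are for benefit and 0.5 for harm. If both supplements truly raised the rate to 0.26 (assumed), both would be significant for harm in 46% of trials, and the 0.02 margin would also be met in 2.7%. Under the planned benefit (0.14, 0.14, 0.20) step 3 is reached in 63%, and the full sequence ends in non-inferiority in about 8%.

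**5. Status of step 3.** Section 9.1 regards it as explorative. Section 9.3.2 places it in a hierarchy adopted for multiplicity, at its own 0.025 level, and downgrades later steps to explorative only if an earlier step fails. The two statements do not agree.

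**The case against.** The case on the other side is substantial.

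- **The unit can be inferred.** Six months is the only unit attached to the rate, and the endpoint and the RUTF versus MNP objective are framed over 6 months. A per-month margin of 0.12 per 6 months is twice the planned effect of 0.06, which hardly fits a slightly worse result. A per-year unit appears nowhere in the analysis section. This stands: the spread from 7% to nearly 100% shows how sensitive the rule is to the unit, not how uncertain a sensible reader would be. What remains is that the margin itself carries no unit.
- **Low power is admitted.** The protocol powers only the comparisons with control and warns that other comparisons may lack numbers. So the 16% is not itself an error.
- **Direction would be read in practice.** The primary hypothesis in section 2 speaks of a reduction, and a non-inferiority claim after two significant harms would be hard to misread. This limits the effect; the written rule still permits it.

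Three stronger readings are tempting, and the protocol does not support them. A reader might infer that the Poisson model cannot yield a rate difference. But section 9.3.1 names no link function; an identity link or a difference derived from the fitted model would serve, and that choice may be left to the SAP. A reader might infer that the type I error is inflated. It is not: the fixed sequence keeps its level whichever direction a significant result takes. A reader might infer that the margin decides whether MNP replaces RUTF. Section 1.5 asks whether micronutrients alone prevent malnutrition, and section 11.3 ties uptake to MNP being effective; both are questions for step 2.

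**Conclusion.** The point holds and is minor. The step 3 margin has no time unit, its hypotheses are reversed against the protocol's own explanation, steps 1 and 2 do not require benefit, and the status of step 3 differs between sections 9.1 and 9.3.2. On the natural 6-month reading, step 3 alone passes in about 16% of trials; the unit could move this to about 7% or nearly 100%. Under no effect, continuation towards harm has a probability of about 2.5% at each step and 0.5% at both.

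These figures assume 0.14 in both supplement arms (0.20 in all arms for the no-effect case), 660 children per arm with full follow-up, and a normal approximation for step 3. The reversal of the hypotheses needs no assumption beyond a higher rate being worse. The primary RUTF versus control test and the stated sample size are unaffected.

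**What to change.** Change the wording of section 9.3.2 before unblinding:

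1. State the margin as 0.02 first events per child per 6 months, the scale of the planned 0.20 versus 0.14. Do not equate this with the 168-day final visit without converting: 168 days is about 5.5 calendar months, so 0.02 per 6 months is about 0.02 × 168/182.6 = 0.0184 per 168 days.
2. Swap the hypotheses: H0 is rate_MNP − rate_RUTF ≥ 0.02 and H1 is rate_MNP − rate_RUTF < 0.02. Conclude non-inferiority when the upper one-sided 97.5% limit of rate_MNP − rate_RUTF is below 0.02.
3. Continue past steps 1 and 2 only if the supplement's rate is significantly lower than control, that is, if the upper limit of the two-sided 95% interval for the rate ratio is below 1.
4. Reconcile sections 9.1 and 9.3.2 on whether step 3 is explorative or a formal, unpowered test in the hierarchy.

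The estimator of the difference can be named in the SAP. The cost is a few lines of text, with no change in significance level or sample size.
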